### Data annotation

3.2

In the crucial phase of data annotation, our study collaborates with the Department of Mental Health at Guangdong Second Provincial General Hospital, enlisting the expertise of five experienced physicians. The data annotation process involved five doctors, each with over 10 years of experience. The dataset was divided equally among them, with each doctor responsible for annotating a specific portion. This approach ensured that the entire dataset was annotated efficiently and effectively, with all doctors completing their assigned tasks until the full dataset was annotated.

The physicians, utilizing their medical expertise and understanding of mental health, carefully review the responses from the various questionnaires, including the STAI, CES-D, and others. The doctors consider several critical aspects of exercise prescription: (1) Type of Exercise: determining the most suitable form of physical activity, whether it’s aerobic, strength training, flexibility exercises, or a combination, based on the participant’s health status and preferences; (2) Frequency: establishing how often the participant should engage in the prescribed exercises, balancing effectiveness with practicality. (3) Intensity: setting the appropriate level of exertion for each exercise, tailored to the individual’s physical capabilities and mental health needs. (4) Duration: recommending the length of each exercise session to maximize benefits while ensuring safety and adherence.

The initial dataset comprised 800 cases, designated as the training set, and a smaller set of 200 cases, set aside as the test dataset. To augment the robustness and diversity of our training dataset, we employed the *ChatGPT* to generate an additional 9,200 simulated samples. This step was based on the patterns and characteristics observed in the initial 800 cases. By doing so, we significantly expanded our dataset, enriching the training process and enhancing the model’s ability to generalize across a broader range of scenarios. This extensive data annotation and augmentation process is crucial for developing an accurate and effective AI-driven exercise prescription system. It ensures that the model is not only trained on a substantial and varied dataset but also fine-tuned to reflect real-world complexities and nuances in mental health and physical fitness.

### Model selection

3.3

In the model selection phase of our study, we employed a multi-model approach to identify the most effective machine learning algorithm for our data. We will rigorously trained and tested various models, including Linear Regression, Decision Trees, Random Forests, Support Vector Machines (SVMs), Neural Networks, Recurrent Neural Network (RNN), and Gradient Boosting Machines (GBMs), each evaluated on accuracy, precision, recall, and F1 score. The process involved using our annotated dataset for training and a separate testing set for validation. Ultimately, the model demonstrating the highest predictive accuracy and robustness on the testing set will be selected. This model, excelling in processing complex mental health data, forms the cornerstone of our AI-driven exercise prescription system, ensuring personalized and effective recommendations for individuals with mental health conditions. In our study, we anticipate that the AI model will achieve an AUC of over 0.9, demonstrating its high accuracy in tailoring exercise prescriptions for mental health improvements.

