### Study design

2.1

In the first phase, we focus on developing a multimodal data-driven intelligent system for exercise prescription. To achieve this, we will initially recruit 1,000 participants for AI model training and testing. Of these, 80% (800 participants) form the training set. To enhance the robustness and generalizability of the AI model, we will use ChatGPT to simulate an additional 9,200 cases based on the initial 800, resulting in a comprehensive training set of 10,000 instances. The remaining 20% (200 participants) will be reserved as a testing set. This diverse dataset will then be annotated by a team of 10 experienced doctors from the Department of Mental Health at Guangdong Second Provincial General Hospital. Their expertise will ensures the accuracy and clinical relevance of the data labeling, which is critical for the development of a reliable and effective AI system.

In our analysis, we will set the effect size at 0.5 to assess the intervention’s effectiveness. This value represents a medium effect size, which is considered substantial in the context of our study. Following the development and preliminary testing of the AI model, the second phase of the study will involves an RCT with 50 participants. These participants are randomly divided into two groups: 25 in the experimental group and 25 in the control group. The experimental group will receives personalized exercise prescriptions generated by the newly developed AI system, while the control group will receives standard exercise recommendations. This phase aims to evaluate the efficacy of the AI-driven exercise prescription system in a real-world clinical setting. The RCT’s design ensures that the results are robust and can be attributed specifically to the intervention, thereby providing strong evidence of the system’s potential benefits for individuals with mental illnesses.

The effectiveness of the AI-driven exercise prescriptions is evaluated at multiple time points: initially at the end of the 6 months trial period (Trial Completion Assessment), followed by a 6 months follow-up assessment and a 12 months follow-up assessment. These assessments are designed to track and compare the short-term and long-term impacts of the AI-driven exercise prescriptions on the mental health outcomes of the participants (shown in Figure 1).

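### The final model is chosen by its score on the 200-case testing set, so its reported phase 1 accuracy is optimistic in expectation and no independent estimate remains

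*Protocol article*

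**What the plan says.** Section 2.1 (Study design) sets out the data: "we will initially recruit 1,000 participants for AI model training and testing". It continues: "Of these, 80% (800 participants) form the training set". ChatGPT is then used to "simulate an additional 9,200 cases based on the initial 800, resulting in a comprehensive training set of 10,000 instances". The rest is held out: "The remaining 20% (200 participants) will be reserved as a testing set". Section 3.2 (Data annotation) repeats the two-way split: "The initial dataset comprised 800 cases, designated as the training set, and a smaller set of 200 cases, set aside as the test dataset".

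Section 3.3 (Model selection) lists seven families, from linear regression to gradient boosting, in an open-ended list, "each evaluated on accuracy, precision, recall, and F1 score". It gives the testing set the role of validation and states the rule: "Ultimately, the model demonstrating the highest predictive accuracy and robustness on the testing set will be selected". It adds an expectation, "we anticipate that the AI model will achieve an AUC of over 0.9", without naming the data on which that AUC would be measured.

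The article describes no validation subset, cross-validation or external test set.

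**The concern.** A held-out set gives an unbiased estimate of performance only if it played no part in choosing the model. Here the 200 cases have two jobs: they decide which candidate wins, and they are the only described data on which the winner's performance could be reported. The winner is partly the best model and partly the model favoured by chance on these 200 people, so its score on them tends to exceed its performance on new patients. Adding robustness to the criterion does not help, because it too is judged on the testing set.

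At stake is the credibility of the phase 1 performance statement. Once the 200 cases have been used for selection, their independence cannot be restored without new data.

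**Working it through.** **1. The plan's own figures.** 0.80 × 1,000 = 800; 0.20 × 1,000 = 200; 800 + 9,200 = 10,000. The split reproduces exactly. All simulated cases go to training, so the testing set stays at 200 real cases.

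**2. Sampling error of one model's accuracy on 200 cases.** SE = √[p(1 − p)/200], where p is the true accuracy. The article gives no value for p, so a range is assumed: 0.0346 at p = 0.60, 0.0324 at 0.70, 0.0283 at 0.80 and 0.0212 at 0.90.

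**3. Rough size for seven equally good, independent candidates.** The expected maximum of seven independent standard normal values is about 1.35, so the optimism is about 1.35 × SE:
- p = 0.60: 1.35 × 0.0346 = 0.047
- p = 0.70: 1.35 × 0.0324 = 0.044
- p = 0.80: 1.35 × 0.0283 = 0.038
- p = 0.90: 1.35 × 0.0212 = 0.029

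**4. Simulation.** Seven candidates are scored on the same 200 cases, the best is kept, and its score minus its own true accuracy is averaged over 20,000 runs. Candidates make shared errors through a latent normal correlation of 0, 0.5 or 0.8 (assumed). Optimism in percentage points:

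| True accuracy of the seven | Correlation 0 | 0.5 | 0.8 |
|---|---|---|---|
| all 0.70 | 4.3 | 3.6 | 2.8 |
| all 0.80 | 3.8 | 3.1 | 2.5 |
| all 0.90 | 2.8 | 2.4 | 2.0 |
| evenly spaced, 0.76 to 0.82 | 3.1 | 2.5 | 1.7 |
| evenly spaced, 0.70 to 0.82 | 2.2 | 1.6 | 1.1 |
| evenly spaced, 0.60 to 0.90 | 0.5 | 0.3 | 0.1 |

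The first column agrees with step 3. With p = 0.60 from step 3 as the upper end, equal candidates give about 2 to 5 points. Unequal candidates give about 0.1 to 3 points.

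**5. AUC, as an upper case only.** If the choice were made on AUC itself, with a binary label at 50% or 20% prevalence and a common true AUC of 0.80 to 0.88 (all assumed), the optimism would be 0.016 to 0.051. With true AUC 0.88 for every candidate, the selected model would exceed 0.9 in about 43% to 88% of runs, against 19% to 27% for one model fixed in advance. AUC is not among the listed metrics, so the actual effect would be smaller, to the extent that AUC and the selection metric diverge.

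**6. After the change in the last section below.** Selection bias on the 200 cases is zero in expectation and only sampling error remains. The 95% half-width for accuracy is 1.96 × 0.0324 = 0.064 at p = 0.70, 1.96 × 0.0283 = 0.055 at 0.80, and 1.96 × 0.0212 = 0.042 at 0.90.

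**The case against.** The strongest reply is that this matters little. Nothing suggests that such different families perform equally well, and if one is clearly best the optimism nearly vanishes. Taking the top scorer is a reasonable way to choose a model; only its reported score suffers. Efficacy is judged in the trial, not by this score. All of this stands, and it limits the size and severity of the point. It does not remove it: the article states the selection rule outright, so this is not detail left to a fuller document, and the rule defeats the purpose for which the 200 cases were held out.

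Four stronger readings are tempting but unsupported.
- **A reader might infer that an inflated figure would wrongly let the model through to patients.** The article sets no threshold or go/no-go rule. The AUC above 0.9 is an expectation, section 2.1 calls this stage preliminary, and the trial simply follows it.
- **A reader might infer that the AUC will certainly be inflated.** The data for the AUC are not named, and AUC is not a listed selection metric. That it would come from the 200 cases is a reasonable inference, no more.
- **A reader might infer larger bias from tuning many settings on the 200 cases.** Nothing in the text says that this will be done.
- **A reader might infer that classification metrics cannot suit a prescription with type, frequency, intensity and duration.** That depends on how the labels are coded, which an article may leave to the full protocol.

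**Conclusion.** The point holds for reuse of the testing set. Followed as written, section 3.3 leaves no independent estimate of the chosen model's performance, and accuracy reported on the 200 cases is optimistic in expectation by roughly 0.1 to 5 percentage points. The lower end applies if one candidate is clearly best, the upper end if seven are equally good with largely unrelated errors. This rests on assumed true accuracies of 0.60 to 0.90 and assumed correlations of 0 to 0.8; the article fixes neither. The bias is an average tendency and need not appear in any single run. It is smaller than the 95% half-width at the same accuracy, but an interval computed in the usual way around the winner's score would not account for it.

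A reader might also infer that the trial result is compromised. It is not: outcomes of the randomised participants play no part in choosing the model, so the between-group comparison is not biased by this rule. The point should be fixed, but it does not threaten the trial's main comparison.

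**What to change.** In section 3.3, replace selection on the testing set with selection and tuning inside the 800 real training cases only. Two routes work:
- Set aside a validation subset of the 800 before any ChatGPT simulation, generate simulated cases from the remainder only, and choose the model on the subset. This is the simpler route.
- Use cross-validation that keeps simulated cases in the same fold as the real cases they came from.

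Then lock one model, score it once on the 200 untouched cases, and report that result with a 95% confidence interval. Describe the AUC expectation as agreement with the doctors' prescriptions on those 200 cases, since the labels are those prescriptions.

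Cost: slightly less data for fitting during selection, some extra simulation and coding work (more under cross-validation than with one validation subset), and a slightly less favourable headline figure. No additional participants are needed.

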## Introduction

1

Mental illnesses, a significant global health concern, encompass a wide spectrum of psychological disorders affecting millions worldwide (1, 2). The ramifications of these disorders extend beyond the individual, affecting families, communities, and economies. For instance, depression alone is a leading cause of disability worldwide, and mental disorders are among the major contributors to the overall global burden of disease (3, 4). The societal impact of mental illness is profound, encompassing economic costs due to lost productivity, healthcare expenses, and the intangible yet substantial cost of reduced quality of life (5, 6). Additionally, mental health disorders can exacerbate social issues such as homelessness and unemployment, creating a vicious cycle of poverty and illness (7).

The field of exercise prescription for mental illness has garnered increasing attention in recent years, as evidenced by a growing body of research. Studies have consistently demonstrated the efficacy of regular physical activity in alleviating symptoms of various mental disorders, including depression, anxiety, and schizophrenia (8–11). For example, a meta-analysis by Rosenbaum et al. indicated that moderate to vigorous physical activity could significantly reduce depressive symptoms in adults (12). Despite these advancements, several challenges and gaps remain in the application of exercise prescription for mental health. A primary concern is the lack of individualization in exercise regimes. Most existing studies and protocols adopt a one-size-fits-all approach, neglecting the unique needs, preferences, and limitations of individual patients (13). This generalized approach may lead to suboptimal outcomes and lower adherence rates, as patients may find the prescribed exercises either too challenging or not engaging enough. Another significant limitation is the scarcity of data-driven methods in tailoring exercise prescriptions. While some studies have begun to explore the use of data in optimizing exercise interventions (14, 15), there is still a considerable gap in integrating comprehensive, multimodal data – such as genetic, physiological, and behavioral information – to inform exercise prescriptions. This lack of integration results in missed opportunities to enhance the precision and effectiveness of exercise as a therapeutic tool for mental health.

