### Intervention measures

4.2

The 25 participants in the intervention group receive personalized exercise prescriptions generated by our AI model. These prescriptions are meticulously tailored based on each participant’s health profile and mental health status. The AI model determines the most suitable Type of Exercise for each individual, ranging from aerobic activities to strength training, depending on their physical and mental health needs. The Frequency of exercise is set, aiming for a balance that maximizes benefit while considering each individual’s lifestyle and capacity. Intensity levels are also customized, ensuring that exercises are challenging yet safe and achievable for each participant. Lastly, the Duration of each exercise session is specified by the AI model, optimizing the time spent on each activity for maximum efficacy. For example, for a participant with moderate depression and a sedentary lifestyle, the AI model might prescribe light aerobic activities like brisk walking or cycling for 30 min, three times a week. The intensity would be set at a moderate level, ensuring the participant can comfortably sustain the activity while gaining mental health benefits. The model may also suggest gentle yoga twice a week to improve flexibility and reduce stress, tailoring the duration to 20 min per session to match the participant’s initial physical fitness level. The intervention lasts for a period of 4 weeks, during which participants adhere to their personalized exercise regimen. The control group, comprising another set of 25 participants, receives standard care practices. This generally includes generic health advice and non-tailored exercise recommendations, reflecting the conventional approach to mental health management. The control group’s treatment does not involve the AI-driven customization of exercise parameters, serving as a baseline to evaluate the effectiveness of the personalized exercise prescriptions provided to the intervention group.

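### The model is chosen on predictive accuracy, which does not secure personalised prescriptions if one label dominates; a class-balanced deciding metric and a commonest-prescription benchmark would close the gap

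*Protocol article*

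**What the plan says.** Section 3.3 (Model selection) of the protocol article names seven types of model, "each evaluated on accuracy, precision, recall, and F1 score". The sentence that decides between them is: "Ultimately, the model demonstrating the highest predictive accuracy and robustness on the testing set will be selected". Robustness is not defined, and the averaging used for precision, recall and F1 across classes is not stated. The section adds an expectation: "we anticipate that the AI model will achieve an AUC of over 0.9". It is not worded as a condition for using the model. The section also says that the chosen model is "ensuring personalized and effective recommendations for individuals with mental health conditions".

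The testing set is fixed in section 2.1 (Study design): "The remaining 20% (200 participants) will be reserved as a testing set". The labels come from section 3.2 (Data annotation), where doctors set type, frequency, intensity and duration for each case.

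Personalisation is the idea under test. The Introduction gives the problem as "Most existing studies and protocols adopt a one-size-fits-all approach, neglecting the unique needs, preferences, and limitations of individual patients". Section 4.2 (Intervention measures) defines the control arm by its absence: the control group's "treatment does not involve the AI-driven customization of exercise parameters".

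**The concern.** Accuracy rewards agreement with the doctors' labels. When one label is much more common than the others, a model gains accuracy by returning that label to nearly everyone, because each departure from it must be right more often than wrong to pay off. The deciding criterion therefore pulls towards uniform output in exactly the situation where personalisation is hardest to learn.

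Nothing else in section 3.3 counters this. No stated criterion compares the model with the rule that gives every patient the commonest prescription, and no stated step looks at how far the issued prescriptions vary. The claim that the selected model ensures personalised recommendations does not follow from the rule.

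At stake is the meaning of two results. A reader shown an accuracy of, say, 85% cannot tell whether that is a 35-point gain over a constant rule (commonest label 50%) or none (commonest label 85%). If the output were close to uniform, the RCT result would say little about individual tailoring, whichever way it fell.

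**Working it through.** **Inputs from the article.** Testing set: 20% of 1,000 = 200. Training set: 80% of 1,000 = 800, plus 9,200 simulated = 10,000. Both reproduce. The AI arm has 25 participants (section 4.1). The anticipated AUC over 0.9 is the only performance figure, and it cannot be reproduced because no inputs are given for it.

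**Assumptions.** The article gives no distribution of the annotated labels. The share p of the commonest label is therefore varied from 50% to 95%, and the AUC from 0.65 to the anticipated 0.90. One prescription component is reduced to two classes: the commonest label and any other. Model scores are taken as normal with equal variance, mean 0 for patients with the commonest label and mean d for the others.

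**Formulas**, with q = 1 − p and Φ the standard normal distribution function:

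- Separation: d = √2 · Φ⁻¹(AUC)
- Accuracy-maximising cut-off: t = d/2 + ln(p/q)/d
- Accuracy: pΦ(t) + q[1 − Φ(t − d)]
- Share of patients not given the commonest label: p[1 − Φ(t)] + q[1 − Φ(t − d)]
- Constant rule: accuracy p, AUC 0.5

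**Example, AUC 0.70 and p = 0.80.** d = 1.414 × 0.524 = 0.742. t = 0.371 + 1.386/0.742 = 2.240. 1 − Φ(2.240) = 0.0125 and 1 − Φ(1.499) = 0.067. Share = 0.8 × 0.0125 + 0.2 × 0.067 = 0.023. Accuracy = 0.8 × 0.9875 + 0.2 × 0.067 = 0.803.

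| AUC | Commonest label (= accuracy of constant rule) | Accuracy of model | Gain, points | Not given commonest label | Of 25 |
|---|---|---|---|---|---|
| 0.65 | 70% | 70.6% | 0.6 | 5.4% | 1.3 |
| 0.70 | 80% | 80.3% | 0.3 | 2.3% | 0.6 |
| 0.75 | 70% | 74.2% | 4.2 | 16.2% | 4.1 |
| 0.75 | 80% | 81.1% | 1.1 | 5.4% | 1.4 |
| 0.90 | 50% | 81.8% | 31.8 | 50.0% | 12.5 |
| 0.90 | 70% | 84.2% | 14.2 | 26.0% | 6.5 |
| 0.90 | 80% | 87.3% | 7.3 | 14.9% | 3.7 |
| 0.90 | 90% | 92.3% | 2.3 | 5.3% | 1.3 |
| 0.90 | 95% | 95.6% | 0.6 | 1.7% | 0.4 |

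Near-uniform output, about 5% or less off the commonest label, thus needs a share of about 70% at AUC 0.65, about 80% at AUC 0.70 to 0.75, and about 90% at AUC 0.90.

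**Would the other metrics show it?** For a constant rule on two classes, F1 for the commonest label is 2p/(1 + p) and F1 for the other is 0. At p = 0.9 macro-F1 is 0.947/2 = 0.47, which exposes the rule. F1 weighted by class size is 0.9 × 0.947 = 0.85, which does not.

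**What a class-balanced criterion would change.** Macro-F1 is the mean over the two classes of 2TP/(2TP + FP + FN). Moving the cut-off to its maximum, found numerically, gives:

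- AUC 0.70, p = 0.80: 21.9% off the commonest label instead of 2.3%; accuracy 74.7% instead of 80.3%.
- AUC 0.90, p = 0.90: 9.9% instead of 5.3%; accuracy 91.3% instead of 92.3%.

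In both cases the model's variation returns to about that of the doctors' own labels (20% and 10%).

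**The case against.** The rule is not accuracy alone. Robustness is part of it, four metrics are computed for every candidate, and the section uses the word accuracy loosely, since it treats a high AUC as a sign of high accuracy. A truly constant model would have an AUC of 0.5 and poor macro-averaged recall and F1, so an investigator who looked at the listed metrics would see it. A constant rule is also not among the candidates. All of this stands as a limit on the concern. It does not remove it, because the deciding sentence names only accuracy and an undefined robustness, and because at AUC 0.9 with a 90% commonest label the winning model is still nearly uniform.

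The label distribution is unknown and may be well spread. With a commonest label of 50% to 70% and an AUC of 0.9, a simulation of 200 test cases puts the constant rule ahead in about 0.2% of runs or fewer. The full prescription has four components: if each had an 80% commonest label and they were independent (an assumption), the commonest full prescription would cover 0.8⁴ = 41% of patients. This stands too, and it makes the finding conditional.

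An article may leave a benchmark or the averaging of F1 to a fuller document. That is fair for those details taken alone. Here, however, a deciding rule is stated together with a property it is said to ensure, and the rule does not deliver that property.

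A reader might infer more: that the AI arm would receive what amounts to the control arm's advice, so that the effect of 0.5 and the power of the RCT would shrink. The documents do not support this. Nothing in sections 4.1 or 4.2 says that the doctors' commonest prescription equals the standard recommendation, so no loss of power can be derived from label concentration.

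**Conclusion.** The concern holds in a conditional form. Selection on accuracy does not secure the personalisation that section 3.3 claims and that the RCT is meant to test. If the labels for a component are strongly concentrated, the selected model can be close to giving everyone the commonest prescription: in the illustration, 0.4 to 1.4 of 25 participants would receive anything else for that component in the concentrated cases. With balanced labels and the anticipated AUC the risk is small.

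These sizes rest on a two-class, equal-variance normal model and on assumed label shares. It would be wrong to conclude that a one-size-fits-all model is likely to win or that the RCT cannot test personalisation, because the article gives no label distribution from which either could be judged. The point is worth acting on because that distribution is unknown and the change is nearly free.

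**What to change.** In section 3.3, for each of type, frequency, intensity and duration:

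- Make macro-F1 or chance-corrected agreement with the doctors' labels the deciding metric, in place of predictive accuracy.
- Report the rule that gives everyone the commonest prescription as a benchmark on the same 200 real test cases, with the paired difference from the selected model and its 95% CI. Both rules are scored on the same patients, so the paired difference is the right comparison, and separate intervals for each proportion are not. The same 200 cases also choose the model, so the difference will be somewhat optimistic and should be read as such.
- Report the distribution of prescriptions that the model issues for the 200 test cases and, later, for the 25 participants in the AI arm.

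A fixed threshold for releasing the model to the RCT is not needed for this point; whether to add one is a trade-off for the sponsor.

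The cost is a few lines of text and an extra analysis of data already planned, with no new participants. There are two downsides. The gain over the benchmark will look smaller than raw accuracy does. The selected model may also have lower raw accuracy: by 92.3 − 91.3 = 1.0 point and 80.3 − 74.7 = 5.6 points in the two illustrated cases, and by nothing when two classes are balanced.
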